### Classical BACI designs and extensions

Because of the temporal nature of health data and the underlying trends caused by the increasing burden of chronic disease with increasing age, before and after comparisons can be difficult or inconclusive. In this study we will have available patient data for a period of 4.5 years including the period of the intervention which may vary from 6–18 months.

Since standard BACI design cannot be used when study variables trend over time, we adopt a mathematical approach using a mixed linear effects model (*lme*) to assess the intervention while trying to adjust for the time varying mean in simple ways. The *nlme* library in the statistical package R is used to perform the analysis according to the methods of Pinheiro et al. [39].

The Test patients will be matched with one or two controls and the relative movement of Test patients’ outcomes before and after the start of the intervention will be compared to that of their Control patients. The before-and-after comparisons use control patients to adjust for background variations in such variables as public health policy impacting on costs and even for example, climatic conditions during the before and after intervention period.

Let *y*_*ijk*_ be any of the variables to be analysed, such as for example, the PBS/MBS/Hospital costs value per unit time period (month) at time k during period *i* (before or after the intervention), for patient *j* (control or intervention patient). The model for the response value is given by

where:

 *μ* is the overall mean *α*_*i*_ is the effect of period (before and after) τ_k(i)_ is the repeated measures within periods (assumed to be a random effect) β_j_ is the effect on jth matched patients (intervention or control) (αβ)_ij_ is the interaction between period and matched patient groups θ is the overall slope relating to time in months if no differentiation is made between the groups (B-A, C-I) θ_ij_ is the slope relating to time (k) in months for the various combinations of the groups (B-A, C-I). e_ijk_ is the random error term of the model that is assumed to be normally distributed with homogeneous variance.

Assumptions made:

 Log of cost plus one will be treated as normally distributed with log of the number of days in the month as the offset. Sometimes the square root transformation may be used to stabilise the variance. We are hoping there are not too many zero cost periods or zero counts. If this fails we will use the zero adjusted inverse Gaussian distribution for the model – fitting them using the **gamlss** (package in R) using random() for including random effects [40]. τ_k(i)_ is a random effect in the above model that is assumed to be normally distributed with mean zero and constant variance. The assumption in the previous dot point and the assumption for e_ijk_ in the model thus assumes that measurements made at the same time segments (e.g., on the same quarter) have the same correlation and homogeneous variances for all repeated measures. The above model treats the study as a fully-designed experiment with the appropriate randomisation. However, this is seldom the case because most impact studies are observational in nature. The assumption is that each measurement for the intervention patients is matched with a measurement for one or more control patients. This blocking is expected to control for the non-randomisation in the design. The complexity of this analysis can be greatly reduced by taking the differences between the Test and Control measurements The model above tests whether a significant change has occurred by testing the significance of the interaction term of the model for the before after indicator variables and the control-intervention indictor variable. For example if the coefficient for intervention patients and after intervention duration has lower insured costs that before the intervention after adjusting for controls, then the intervention has had a significant impact on costs. The random effects terms and random error term are assumed to be uncorrelated in time. The control patient is generally selected to control for all covariates. In this study this means that control patients should be identical to the intervention patient in terms of age, gender, SEIFA index and major comorbidities. The samples are selected over time (therefore they are time series rather than repeated measures made at the same time). So it may seem unlikely that the model errors will be independently distributed but hospital costs are measured a month apart and this should be enough to for the assumption of independence to be valid. The assumption that all repeated measures have the same variance is unlikely to be true. If the gamlss package is used then this change in variance can be accounted for. Although theoretically longitudinal data structures can be modelled by random effects in gamlss [40] but at present no computationally feasible implementation for large sample sizes and complex models exists. Assume that the trend in the response variable over time is approximately linear. This assumption is likely to be reasonable over the 5 year study period, but is unlikely to be true for longer time periods.

These models will be fitted using the nlme package in R [39].

A hypothetical scenario is modelled schematically in Figure 5 below according to principles and assumptions outlined above.

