**Table 2 Tab2:** **Example of case matching of Control patients with Test patients**

Test/control	Age	Gender	Major diagnosis	Seifa ^1^ index for postcode	Strength of match (perfect match = 0)
Test	54	M	COPD	1023	
Control	56	M	COPD	1025	1.68^2^
Control	54	F	HD	1022	2.16^3^
Weights	0.2	1	1	0.16	

^1^SEIFA 2011 Socio-Economic Indexes for Areas [24]. SEIFA provides measures of socio-economic conditions by geographic area.

^2^|54-56| × 0.2 + 1 × 0 + 1 × 0 + |1023-1015| × 0.16 = 1.68.

^3^|54-54| × 0.2 + 1 × 1 + 1 × 1 + |1023-1022| × 0.16 = 2.16.

Generally, the closer the match the greater the likelihood of finding a significant result with a smaller number of samples if the impact is relatively small.

Ideally, as many as four matches are sought for each Test patient, and the closest match is then selected as the case matched control for that Test patient. In many cases only one acceptable match may be available.

Following a change of Government in Australia, the requirement to connect patients to the high speed National Broadband Network was removed and as consequence, approximately half of our trial patients will be connected to a variety of NBN, ADSL, ADSL2 and VDSL network services with a minimum level of service of 2Mbps download and 1Mbps upload. Those on the NBN service were guaranteed a download speed of 25Mbit/sec and an upload speed of 5Mbit/sec.

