All statistical tests for the before intervention period will be two-sided but all tests of whether the intervention made a difference will involve a one-tailed matched pair t-test, and either a p value of 0.05 or less will be used to indicate statistical significance or a confidence interval will be provided to judge the impact of the intervention. Statistical analysis will be performed using Stata Release V.12 (TX: StataCorp LP), SPSS 17, R package [38] and Microsoft Excel.

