**Figure 5 Fig5:**
[figure not shown]
**Output of lme modelling of mean monthly MBS cost per patient for test and control.** Patients based on hypothetical data. Each monthly data point is plotted as a box and whiskers plot representing data for the 125 Test patients and 250 Control patients.

The BACI analysis will be carried out using the statistical modelling package R [38]. The output will provide an estimate of the correlation between Test and Control data and will provide best fits, standard errors, t-values and p-values for all model parameters before and after the intervention.

In the schematic diagram above we would expect very little difference between Test and Control patients in either the slope or the intercept of the model prior to the start of the intervention. The hypothetical model in Figure 5 shows that the impact will result in a change of the historical slope of the model before the intervention for Test patients, representing a time dependent fall in Mean Monthly MBS Costs, whilst there is no corresponding change in the slope for Control patients after the intervention.

Modelling of the available data will reveal underlying time dependent trends associated with the ageing process as well as the impact of the intervention and will allow an estimate to be made of savings associated with the impact of the intervention.

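### Exposure may run from 6 to 18 months and the effect is expected to grow with time, yet the two decision tests and the savings estimate are tied to no exposure time

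*Protocol article*

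**What the plan says.** The section on classical BACI designs and extensions states that patient data cover 4.5 years, including "the period of the intervention which may vary from 6–18 months". It gives no distribution of exposure and no reason for the variation.

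The text with Figure 5 describes the expected impact, for a hypothetical cost outcome, as a changed slope in Test patients, "representing a time dependent fall in Mean Monthly MBS Costs", with no matching change in Controls. It then promises an estimate of savings and states no duration for it.

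Two decision rules are given:

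- Data analysis: "all tests of whether the intervention made a difference will involve a one-tailed matched pair t-test", and "a p value of 0.05 or less will be used to indicate statistical significance" unless a confidence interval is given instead.
- Classical BACI designs and extensions: the mixed model judges change by "testing the significance of the interaction term of the model for the before after indicator variables and the control-intervention indictor variable". The example that follows reads a lower value of this coefficient as an impact on costs.

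The same section lists slopes by group and period (θ_ij) among the model terms and assumes an approximately linear trend.

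**The concern.** If the effect builds up month by month, its size has a meaning only together with a time on telemonitoring. A single before/after contrast then depends on how long each patient happened to be monitored. Two trials with the same true effect but different exposure mixes would report different effects and savings.

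The interaction raises a separate problem. Once slopes by group and period are in the model, the indicator interaction is no longer an average after-period effect. It is the Test-Control gap, after minus before, extrapolated to the point where time equals zero. The article does not say where that point lies.

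The stake is the reading of the result. A reported effect or saving would be hard to attach to any stated duration of service, and the interaction test could miss a real slope change or reverse its sign.

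**Working it through.** **The plan's own figures.** The only related numbers are the Table 6 powers, at an effective sample size of 30. The article's text gives no values for the standard deviation or the correlation, so they cannot be recomputed. Back-solving a one-sided 5% paired t-test for admissions (shift 0.5, power 0.99) gives an SD of about 0.67. Exposure does not enter these calculations.

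**Inputs.** Exposure T is 6 to 18 months, the number of Test patients is 125, and the data span is 4.5 years = 54 months (all from the article). Assumed for illustration: the effect is m units in month m after the start, and exposure is a whole number of months.

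**Step 1: average over the whole after period.** The mean of 1, 2, ..., T is (T+1)/2.

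- T = 6: 7/2 = 3.5
- T = 12: 13/2 = 6.5
- T = 18: 19/2 = 9.5

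The ratio of longest to shortest is 9.5/3.5 = 2.7.

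**Step 2: average over patients.** With w_T the share of patients having exposure T, equal weight per patient gives Σ w_T (T+1)/2. Equal weight per patient-month gives Σ w_T T(T+1)/2 divided by Σ w_T T. The mixes are assumptions.

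| Assumed mix | Patients equal | Patient-months equal |
|---|---|---|
| 6 to 18 months equally likely | 6.5 | 1105/156 = 7.1 |
| Half at 6, half at 18 | 6.5 | (21+171)/(6+18) = 8.0 |
| 80% at 6, 20% at 18 | 0.8×3.5 + 0.2×9.5 = 4.7 | (16.8+34.2)/8.4 = 6.1 |
| 20% at 6, 80% at 18 | 0.2×3.5 + 0.8×9.5 = 8.3 | (4.2+136.8)/15.6 = 9.0 |

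One true effect gives 4.7 to 9.0.

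**Step 3: what the interaction estimates.** Let Test patients change by δ per month from onset, with no other difference. Let t be months since onset and u = t - c be model time, with its zero c months after onset. The after-period gap is δt = δc + δu. With θ_ij in the model, the interaction is therefore δc and the slope contrast is δ. For δ = -1:

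| Time zero | Interaction | Slope contrast | Gap at month 6 |
|---|---|---|---|
| At onset (c = 0) | 0 | -1 | 0 + 6×(-1) = -6 |
| Month 9 (c = 9) | -9 | -1 | -9 + (-3)×(-1) = -6 |
| 36 months before onset (c = -36) | +36 | -1 | 36 + 42×(-1) = -6 |

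A noise-free least-squares fit gave the same interactions and slope contrasts. The value c = -36 is plausible: it is the start of a 54-month series for a patient with 18 months of intervention (54 - 18 = 36). There a true fall produces a positive interaction. With zero at onset, the interaction is nil. The slope contrast and the gap at a stated month do not move.

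**Step 4: how many patients remain.** If all exposures from 6 to 18 are equally likely, 125 × (19 - m)/13 Test patients contribute at month m ≥ 6: 125 at month 6, about 115 at month 7, 67 at month 12, 38 at month 15 and 10 at month 18. With half at 6 and half at 18, about 62 contribute from month 7 on. The article does not say which pattern applies.

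**The case against.** The strongest reply is that the article already moves past a simple average. It says the standard BACI design fails when variables trend, models monthly values, and allows slopes to differ by group and period. Under the stated linearity, the effect per month is then defined whatever the length of exposure. It also never says that the t-test uses whole after-period means: it speaks of monthly differences, and Table 6 is on a monthly scale. Finer reporting detail may sit in an analysis plan.

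Most of this is right, but it does not settle the matter. The slopes are in the model, yet the test is placed on the indicator interaction, which step 3 shows to be arbitrary under a pure slope change. The t-test has no slope term, and the months that enter it are not fixed. A saving needs a horizon even when the slope is well estimated.

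A reader might go further and infer that the later months rest on an unrepresentative group: early recruits enrolled before "the requirement to connect patients to the high speed National Broadband Network was removed". The article does not show this. It gives no enrolment dates, no common end date and no statement that connection type alters the outcome, and NBN is among the services listed after the change. In an illustrative simulation (slope SD 0.5), patients followed to month 15 or later had a mean slope of -0.99 against -1.00 overall when exposure was unrelated to response. It was -1.40 when exposure was made to depend on response. Bias is possible, but not established.

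Nor does the Figure 5 legend, "Each monthly data point is plotted as a box and whiskers plot representing data for the 125 Test patients and 250 Control patients", amount to an error. The data are declared hypothetical, and the figure is schematic.

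**Conclusion.** The point stands as a mismatch between the expected effect and the declared tests. Exposure may vary threefold and the expected impact is a slope change. The decision rules are an interaction whose value depends on the time origin and a paired test with no exposure window, and the saving has no horizon.

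The 3.5 and 9.5 units assume linear growth from the start and a paired test on the whole after period. The range 4.7 to 9.0 rests on assumed exposure mixes. The interaction result assumes a pure slope change and θ_ij in the model as listed.

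It is certain only that fewer patients contribute after month 6 if any stop before month 18. How many fewer, and whether those remaining differ, cannot be told from the article. A reader might also conclude that the results would be useless for funding decisions. That goes too far, because the slope contrast can be recovered from the planned model. The results as declared would be hard to interpret for a stated duration.

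**What to change.** - Count time from each matched set's own start date, and say so in the model definition.
- Declare one test: either the after-versus-before slope contrast between Test and Control, or the model-based Test-Control contrast at a common 6 months using all matched sets. With time zero at the start, the latter is the interaction plus 6 times the slope contrast, so it also captures an immediate step.
- Base the paired t-test on the common first 6 months.
- Report the effect and the saving at 6 months and, as secondary, at 12 months from the model, with the number of sets contributing at each.
- State why exposure varies.

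Six months is already an assessment point for two instruments in Table 4. The change is to analysis and reporting wording only, with no new data. The cost is less precise estimates beyond 6 months, and later benefit does not enter the common-window test. The slope contrast and the 12-month estimate continue to rest on the linearity that the article already assumes.

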**Table 1 Tab1:** **Clinical criteria for eligibility**

Criteria	Type	Description
Age	Inclusion	50 years old and over at consent.
Cognitive capacity	Inclusion	Abbreviated Mental Test (AMT) [23] score >7.
Unplanned acute admissions	Inclusion	A rate of unplanned acute admission with the required principal diagnosis code(s) indicated below:
		a) ≥2 in the last 12 months, or
		b) ≥4 in the previous 5 years.
ICD-10-AM principal diagnosis code(s) for each unplanned acute admission	Inclusion	Code(s) for each unplanned acute admission indicate a diagnosis for one or more of the following chronic conditions:
		a) Chronic Obstructive Pulmonary Disease (J41 – J44, J47 and J20, with secondary diagnosis of J41-J44, J47),
		b) Coronary Artery Disease (I20 – I25),
		c) Hypertensive Diseases (I10 – I15, I11.9. Note: Hypertensive Heart Failure (I11.0) is included in Congestive Heart Failure),
		d) Congestive Heart Failure (I11.0, I50, J81),
		e) Diabetes (E10 - E14),
		f) Asthma (J45).
Unsuitable conditions	Exclusion	The study team considers the presence of the following conditions to be unsuitable for participation in the study:
		a) Any form of cancer,
		b) Any neuromuscular disease
		c) Any psychiatric conditions.
Care team	Inclusion	The eligible patients must be under the care of any of the following:
		a) General Practitioner
		b) Community Nurse
Care programs	Inclusion	Participation in one of the following government care programs:
		a) Commonwealth Chronic Disease Management
		b) Commonwealth Coordinated Veterans’ Care Program
		c) NSW Connected Care Program
Unsuitable care programs	Exclusion	Participation in one of the following government care programs:
		a) Commonwealth Extended Aged Care in the Home

For the purposes of our study unplanned admissions are all admissions other than:Admissions from the waiting list (including both the surgical list and the medical waiting list);Admissions listed as "regular same day planned admissions" which are admissions that are intended regular and planned same‒day admissions for an on‒going phase of treatment, such as renal dialysis or chemotherapy.

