**Table 6 Tab6:** **Power calculations for some selected variables**

Outcome measure all on the monthly scale	Effective sample size?	Assumed normal distribution	Shift amount (K)	SPower
PBS Total cost	30	Log(PBS Total cost+1)	1	1.00
MBS out of hospital costs	30	Log(MBS out of hospital costs+1)	1	1.00
MBS in hospital costs	30	Log(MBS in hospital costs+1)	1	0.84
Number of hospital admissions	30	Square root the number of hospital admissions	0.5	0.99
Number of GP visits during working hours	30	Square root of number of GP visits during working hours	0.5	0.89
Number of GP visits outside of working hours	30	Square root of number of GP visits outside of working hours	0.1	0.50
Total number of GP visits	30	Square root of total number of GP visits	1	0.97
Total number of either Specialist, Psychiatric, Allied Health visits and Procedures	30	Square root of total number of either Specialist, Psychiatric, Allied Health visits and Procedures	1	0.77
Total number of Laboratory tests	30	Square root of total number of Laboratory tests	1	0.97
Number of Laboratory	30	Square root of number of Laboratory	1	0.96
Tests		Tests		

The actual results may be much more complicated than this because the differences between the outcome variables may be auto correlated. This is particularly true if the test patient and the matched control patient outcome measures have different time series trends. Testing of whether the matched differences are auto correlated will be carried out when data becomes available but is not expected to be a significant problem.

The actual results may be much more complicated than this because the differences between the outcome variables may be auto correlated. This is particularly true if the test patient and the matched control patient outcome measures have different time series trends. Testing of whether the matched differences are auto correlated will be carried out when data becomes available but is not expected to be a significant problem.

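### Monthly admissions and costs are modelled as transformed normal data with zeros left to hope; near the entry thresholds most admission months are zero, and the log-scale effect is not a saving in mean dollars

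*Protocol article*

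**What the plan says.** Under Classical BACI designs and extensions, the response is a cost or count per patient per month, fitted with nlme in R. The residual "is the random error term of the model that is assumed to be normally distributed with homogeneous variance". For costs: "Log of cost plus one will be treated as normally distributed with log of the number of days in the month as the offset". The alternative is: "Sometimes the square root transformation may be used to stabilise the variance". Table 6 uses the square root for every count outcome and is headed "Outcome measure all on the monthly scale".

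On zeros, the assumptions list says: "We are hoping there are not too many zero cost periods or zero counts". If this does not work out, it turns to a zero-adjusted inverse Gaussian in gamlss with random effects. Later in the same list, on longitudinal random effects in gamlss, it says that "at present no computationally feasible implementation for large sample sizes and complex models exists". The section then returns to nlme.

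The Data analysis section separately expects many zeros and offers a delta-lognormal distribution (a lognormal for positive values plus a mass at zero) with confidence limits. It does not connect this to the BACI model.

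The assumptions list reads a lower interaction coefficient directly as an impact on costs. The text after Figure 5 says the modelling "will allow an estimate to be made of savings associated with the impact of the intervention".

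**The concern.** Three things do not fit together.

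- **Zeros.** Patients enter through a minimum of "≥2 in the last 12 months" or 4 in 5 years. Cut into months, such histories are mostly zeros for patients near those minima. No transformation turns a mass at zero into a normal variable with constant variance.
- **Fallback.** The stated alternative has a continuous positive part, so it cannot represent counts of admissions or visits. The plan gives no criterion for switching to it and itself doubts its longitudinal form.
- **Estimand.** A saving is a difference in mean dollars. With many zeros, the interaction on log(cost + 1) mainly reflects how often any cost occurred. Its size depends on the unit of money, and its sign need not agree with the change in mean cost.

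Unscheduled admissions and cost-effectiveness are stated objectives, and the Discussion says the trial is meant to inform government funding. Intervention tests are one-tailed, so an apparent fall that is not a fall in mean cost could be counted as success.

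**Working it through.** **Inputs from the protocol.** Entry thresholds of 2 qualifying unplanned admissions in 12 months or 4 in 5 years (Table 1); monthly analysis (BACI section, Table 6); 375 participants and 4.5 years (54 months) of data. No observed admission rate, zero share or cost distribution is given.

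**The plan's own figure.** Table 6 gives power 0.99 for admissions (square-root scale, shift 0.5, effective n = 30). It cannot be reproduced because no value for the SD appears in the text at hand. Back-solving a one-sided paired t-test at 0.05 with 29 degrees of freedom gives an implied SD of about 0.67. For scale: if monthly admissions are Poisson at 2 per year, the square root of the count has mean 0.159 and skewness 2.0. A mean of 0.5 needs about 7 admissions per year. This is context only; the conclusion does not rest on it.

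**Step 1: share of months without an admission.** Two formulas: 1 - rate/12 (each admission in its own month) and exp(-rate/12) (Poisson).

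| Admissions per year | Separate months | Poisson |
|---|---|---|
| 0.8 (4 in 5 years) | 56/60 = 93.3% | 93.6% |
| 2 (2 in 12 months) | 10/12 = 83.3% | 84.6% |
| 3 | 75.0% | 77.9% |
| 4 | 66.7% | 71.7% |
| 6 | 50.0% | 60.7% |

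The share falls to 80% at 2.4 per year (separate months) or 2.68 per year (Poisson).

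**Step 2: the square root.** The square roots of 0 and 1 are 0 and 1, so a 0/1 count is unchanged and its variance stays p(1 - p). At p = 2/12 this is 0.167 × 0.833 = 0.139; at p = 4/60 it is 0.067 × 0.933 = 0.062. The variances differ by a factor of about 2.2, and the transformation does nothing about it.

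**Step 3: log(cost + 1) against mean cost.** Assumed figures, not from the protocol: 15% of months carry a hospital cost of $5,000 in one condition; 12% carry $7,000 in the other.

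- Mean cost: 0.15 × 5,000 = 750 and 0.12 × 7,000 = 840. Ratio 840/750 = 1.12, a 12% rise.
- Log contrast in dollars (the +1 is negligible here): 0.12 × ln 7,000 - 0.15 × ln 5,000 = -0.215; exp(-0.215) = 0.81, read as a 19% fall.
- Same costs in cents: 0.12 × ln 700,000 - 0.15 × ln 500,000 = -0.353; exp(-0.353) = 0.70, read as a 30% fall.

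A second assumed case: a fixed cost of $5,000, with costed months falling by 20% from 1/6. The true mean ratio is 0.80. The ratio from the log contrast is 0.65, 0.75 or 0.88 when the added constant is $0.01, $1 or $100.

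The error can go the other way. With lognormal positive costs (log SD 1), 10% more costed months and 20% lower cost per month, mean cost falls 12% (1.1 × 0.8 = 0.88) but the log contrast gives a ratio of 1.11.

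**Step 4: size of the fallback model.** 375 × 54 = 20,250 patient-months, with slopes by period and group.

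**The case against.** A reader might infer that the eligibility rule forces more than 80% of all patient-months to be zero. It does not. The criteria are minimum numbers of admissions, so they put no floor under the zeros: sicker patients have fewer zero months. They also count only unplanned admissions with listed principal diagnoses, and other admissions add non-zero months. What stands is that zeros stay common well above the thresholds. To fall below 80% over 54 months, a patient needs at least 11 separate admission months (0.20 × 54 = 10.8).

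A reader might also infer that the plan declares its own fallback infeasible. The remark is limited to large samples and complex models, and the plan does not say this trial is such a case. It also notes that taking Test-minus-Control differences simplifies the analysis. That 20,250 patient-months with group-by-period slopes would qualify is plausible but an inference. The missing trigger and the mismatch with counts do not depend on it.

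The plan does provide for zeros elsewhere. The delta-lognormal in Data analysis is a two-part model that can yield mean cost, so it goes too far to say that the planned methods cannot give savings. But that model is not tied to the BACI comparison, and it too is for continuous amounts. As stated, the log-scale interaction does not give the saving. An unseen analysis plan might supply the retransformation; this article, however, already reads the coefficient as the impact on costs.

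Nor do the documents show heavy zeros for PBS costs, out-of-hospital MBS costs, GP visits or laboratory tests. The dollar examples show what is possible, not what is likely.

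Finally, Data analysis names one-tailed matched-pair t-tests for all intervention effects, so the mixed model's place as the main analysis is itself unsettled. Those t-tests also rest on normalising transformations, so the problem remains.

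**Conclusion.** The point holds in a limited form and should be settled before analysis. For admissions, and by extension in-hospital costs, a normal equal-variance model on the square-root or log(cost + 1) scale is poorly suited to patients near the entry thresholds, where about 83% to 93% of months are zero. At 4 admissions per year the share is still about 67% to 72%. These shares assume separate admission months or a Poisson process; the true rate in this cohort is not given. Counts have no suitable zero-handling model anywhere in the document. For costs, the interaction as the plan reads it is not a mean-dollar saving. It changes with the currency unit and, under the assumed costs shown, can point the wrong way.

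**What to change.** - **Admissions and visit counts:** prespecify a negative-binomial or quasi-Poisson model with log days at risk as offset. Keep the period-by-group interaction and the matched-set structure, and report rate ratios with 95% CIs. Use patient-level counts, because averaging two controls produces non-integers.
- **Costs:** prespecify a model for the arithmetic mean. Either place the two-part model from Data analysis inside the BACI comparison and recombine it to mean dollars, or use a log-link gamma or Tweedie model. A gamma likelihood does not admit zeros, so with gamma they need a separate part or a quasi-likelihood fit. Report the mean saving with a 95% CI bootstrapped over matched sets.
- **Log(cost + 1):** keep as a sensitivity analysis, with the currency unit stated and no reading as a saving.
- **Model choice:** replace the hope about zeros and the open-ended switch with these fixed choices, and say whether the mixed model or the matched-pair t-test is the main analysis.

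The cost is analysis-plan wording and modest extra analysis work, including the bootstrap. It needs no new data or participants and uses standard procedures in the software already named.
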